### Intervention

The sensor-equipped insole (Medixfeet Insole®, Thorsis Technologies GmbH, Magdeburg, Saxony-Anhalt, Germany) features six temperature sensors that measure the foot temperatures at different locations. These are the plantar hallux (D1), the first, third, and fifth metatarsal heads (MTK1, MTK3, and MTK5), the mid-foot (lateral), and the heel (calcaneus). From our previous experience considering both energy and performance aspects, the duration of each single measurement is set at 3 min using a measuring frequency of 2 Hz. The measured temperature data will be transferred via Bluetooth® to a smartphone.

For this study, an alarm algorithm with five alarm levels was developed that can be visualized on both the study server (for the physician) and the SPDFA (for the patient). In the algorithm, a “warning signal” will be prompted if temperature differences are > 1.5 °C between left and right corresponding sensor sites (Fig. 4). The following levels have been implemented: level 0 = no “warning signal”; alarm level 1 = first “warning signal”; alarm level 2 = second “warning signal” after at least 4 h; alarm level 3 = third “warning signal” after at least 20 h; alarm level 4 = fourth “warning signal” after at least 32 h. Only the study physician can reset alarm level 4 to level 0 after evaluation. Other eventful alarm levels (levels 1–3) will automatically reset to level 0 if the initially detected “warning signal” is no longer reinforced. The above-mentioned alarm level is not one sensor-specific alarm but reflects the highest alarm level of all six pairs of sensor sites. Based on these alarm levels, the intervention measures vary from physician to patient.

**Fig. 4 Fig4:**
[figure not shown]
Alarm algorithm and related intervention measures. In the algorithm, a “warning signal” will be prompted if temperature differences are > 1.5 °C between left and right corresponding sensor sites. The following levels have been implemented: level 0 = no “warning signal”; alarm level 1 = first “warning signal”; alarm level 2 = second “warning signal” after at least 4 h; alarm level 3 = third “warning signal” after at least 20 h; and alarm level 4 = fourth “warning signal” after at least 32 h. Alarm level 4 encompasses that the study physician interprets the alarm. Other eventful alarm levels (“noticeable,” “confirmation,” or “intervention”) will be automatically reset, if the previous “warning signal” disappears. The related intervention measures include (1) reminding the patient of regular foot care and temperature measurements (every alarm level), (2) performing foot photo documentation (alarm level 3 and 4), (3) interpreting warning signals (alarm level 4), (4) prescribing an intervention period of five days foot relaxation and reduction in daily activities, and (5) recording patients’ interactive feedback during this period

For the physician, on the study server side, the first notification for the physician will occur at alarm level 3. This means that the alarm has to be confirmed in repeated measurements for at least 24 h. At alarm level 4, the physician will interpret the temperature data together with the patient’s past temperature recordings, foot photos (Fig. 5), the interactive diary (Fig. 6), medical history, and laboratory data. If the alarm is confirmed to be a true positive ulcer alarm, the physician will prescribe an intervention period via server that requires the patient to relax his foot and to reduce daily activities for five days. In the case of an assumed “false positive alarm,” the physician will reset the alarm level 4 to level 0.

**Fig. 5 Fig5:**
[figure not shown]
*Flow diagram* to take a photo series (four pictures) of each foot from the plantar and dorsal sides. The foot mask helps the patient to capture standardized foot images. Additional features such as a countdown function and a supporting selfie-stick are implemented to simplify the process especially in elderly patients with physical impairments

**Fig. 6 Fig6:**
[figure not shown]
*Flow diagram* on health self-evaluation within the SPDFA. The interactive wellbeing score is based on the standard WHO-5 questionnaire30, which contains five items: mobility, self-care, usual activities, pain/discomfort, and anxiety/depression. Additionally, the assessment of foot status helps the patient to record the precursors of ulcer development, such as redness, blister formation, pressure sores, lacerations, pain, inflammation, and any other wounds

In contrast, on the SPDFA, the patient will be reminded to perform foot inspection and temperature measurements at every alarm level. At the respective alarm levels (1–3), the patient will receive a classification result as “uneventful.” Then, at alarm level 3, the patient will be asked to take a photo series (four images; of each foot from the plantar and dorsal sides; Fig. 5). At alarm level 4, the patient will be informed that his measurements will be interpreted remotely by the physician. If the physician recommends an intervention from the server, the patient will be continuously informed to relax his foot and to reduce daily activities for five days. The patient will also be requested to confirm that he follows the advice to relax his feet and reduce daily activities with an interactive dialog and a countdown sequence.

Following the five-day intervention, the physician will evaluate the collected data together with the patient’s feedback and the foot images taken on the last day during this period. Depending on this evaluation, the physician will determine whether another intervention period is required or if a doctor’s visit is needed.

### Control group

Patients randomized to the control group will be educated for optimal foot care by a study physician at the entry into the study and will be supported on any aspects of foot care during the study course.

At the study visits at 6, 12, 18, and 24 months, the same interviews and physical examinations as the intervention group will be performed to determine the foot status and possible ulcer formations.

### Adherence to the treatment plan

For patients in the intervention groups, the transmitted data of the intelligent insole is automatically stored in the study server. If no data are collected for seven days in a row or < 17% of all measurement points within a three-month observation period, the server generates a note for the study team. Thus, it can be clarified by telephone callback or in the context of the study plan why data were not collected.

### Intervention provider

The study coordinator and the study advisor are both physicians with > 2 years of professional experience as practicing physicians in internal medicine and diabetology. All other physicians involved in the study have professional expertise and experience in the conduct of clinical studies. The principal investigator and the study coordinator are responsible for staffing and training of the study team. All study-specific responsibilities are defined and authorized in the delegation log by the principal investigator. The training activities are documented in a training log.

### Outcome measures

#### Primary outcome measure

The primary outcome is occurrence of foot ulceration at any point during the 24-month study after visit 0. The severity level of foot ulcerations is classified according to the Wagner-Armstrong classification [30]. Any lesion will be considered as an ulcer in the sense of the primary endpoint (≥ Wagner level 1). Primary endpoints are also assessed according to time to onset of event and to the total number of events (ulceration) in the groups.

#### Secondary outcome measures

The following have been defined as secondary outcomes:
Adherence to the daily two-time temperature measurement based on data acquisition with the appReport on alert frequency in the intervention group based on data acquisition with the appDetection of slow temperature drops as an indicator of blood supply disorders (at daily intervals temperature changes are recorded and evaluated by the study physician: when temperature in the forefoot or whole foot drops considerably compared to the contralateral sensor data (> 1.5 °C) and reach ambient temperature levels an additional visit to the study center will be initiated to test for changes of blood supply) safety-relevant instructions concerning diabetes, the equipment (insole) or others that are evaluated by the study protocol: frequency of AEs and SAEsPrecursors of the primary endpoint: redness, infections, or wounds in the foot area (the precursors are recorded by AEs/SAEs reports, follow-up and unscheduled visits, as well as patient’s report through photo documentation of the SPDFA)Quality of life according to the WHO-5 score [31, 32] at visits 1, 2, 3, and 4

### Sample size

Based on previously reported studies, we assumed a 20% ulcer occurrence rate over two years to be a conservative estimate for the control arm (where in case of a higher occurrence rate, the sample size becomes smaller) [15, 33, 34]. For the estimation of the treatment effect, we assumed a hazard ratio of 2.8 in accord with the study of Armstrong et al. [15]. Sample size calculations by use of log-rank test were based on a type I error probability of 5% (two-sided) and a power of 80%, with a drop-out rate of 20% over a two-year follow-up period per patient. This resulted in a calculated required number of cases of 147. Therefore, we plan for an inclusion of 150 patients for the intervention arm (300 patients in total). Sample size calculation was performed using the software nQuery + nTerim 4.0 (Statistical Solutions Ltd., 2015).

### Statistical analysis

#### Primary endpoint

The primary endpoint “time to onset of the first ulcer” will be analyzed using Cox regression for the intention-to-treat population. Regressors are the treatment arm, age (in years), gender, risk class, and degree of neuropathy. The decisive test is the test adjusted to the other influencing variables for the influence of the therapy arm (a = 0.05, two-sided). The adjusted hazard ratio of the treatment, including a 95% confidence interval, is calculated as the corresponding effect estimator. Secondary analyses pertain to the same analysis but in the per-protocol population.

In addition, in the intention-to-treat population, the ulceration rates for both treatment arms and the associated odds ratio are determined using the Mantel-Haenzel test with the risk class as stratification, whereby the patients are included in the analysis regardless of the actual follow-up period. In addition, the highest Wagner classifications of an ulceration observed for each patient (possibly 0 if no ulceration) are compared between the two therapy arms using the Mann–Whitney U-test, whereby these analyses are performed separately for the two risk classes.

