### Randomization

In the University Clinic for Nephrology and Hypertension, Diabetes and Endocrinology, randomization is performed using the software RITA (from Statsol, Lübeck). Three hundred patients will be assigned to two groups with a 1:1 ratio based on a stratification according to the prevalent risk group (2 or 3), gender, age (< 60 years vs ≥ 60 years), and the degree of neuropathy (restriction of vibration sensation, using the minimization algorithm of Pocock and Simon [29]). Randomization to the study protocol will be based on the intention-to-treat principle. The randomization is not concealed to the physicians and to the study population at any time after informed written consent of the patients.

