#### Secondary endpoints

The precursors of ulceration are analyzed analogously to the primary endpoint.

The score values of the quality of life at the different time points are analyzed by means of mixed models for repeated measurements, whereby the four stratification factors from randomization (risk group, gender, age and the degree of neuropathy) are also included as influencing variables in addition to the therapy arm. The main comparison refers to the time of 24 months.

AEs and SAEs are recorded separately by treatment arm and risk class. In logistic regression models, a comparison between the therapy arms (insofar as the type of AEs/SAEs is not coupled to the experimental therapy arm) is made with the occurrence of at least one event per patient as the target and the same influencing variables as in the analysis of the primary endpoint.

The usage data of the insoles and the corresponding app are first extracted for the patients of the experimental arm from the automatic machine recordings and aggregated in the sense of the corresponding secondary endpoints ([name]. med. [name], Institute for Biometry and Medical Informatics, Otto-von-Guericke-University Magdeburg).

All analyses are carried out using the software packages SAS or SPSS.

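### The supplementary any-ulcer odds ratio is stratified by risk class only and omits three of the four minimisation factors, which makes its test slightly conservative and pulls the estimate towards 1

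*Protocol article*

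**What the plan says.** All references are to the Protocol article.

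- **Randomization:** patients are allocated 1:1 by Pocock-Simon minimisation, with "stratification according to the prevalent risk group (2 or 3), gender, age (< 60 years vs ≥ 60 years), and the degree of neuropathy".
- **Statistical analysis, Primary endpoint, main analysis:** time to first ulcer is analysed by Cox regression. "Regressors are the treatment arm, age (in years), gender, risk class, and degree of neuropathy". This carries the trial's conclusion: "The decisive test is the test adjusted to the other influencing variables for the influence of the therapy arm".
- **Same section, supplementary analysis:** ulceration rates and an odds ratio comparing the arms, which "are determined using the Mantel-Haenzel test with the risk class as stratification". Length of follow-up plays no part in this analysis. Each patient's highest Wagner grade is then compared by Mann-Whitney test within each risk class.
- **Statistical analysis, Secondary endpoints:** in the quality-of-life mixed model, "the four stratification factors from randomization (risk group, gender, age and the degree of neuropathy) are also included as influencing variables". Adverse events and serious adverse events, coded as at least one event per patient, go into logistic models with "the same influencing variables as in the analysis of the primary endpoint". Precursors of ulceration follow the pattern of the primary endpoint.

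**The concern.** Two yes/no outcomes per patient are handled differently without a stated reason. Having any adverse event gets a logistic model with all four allocation factors. Having any ulcer gets a Mantel-Haenszel analysis with one.

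Minimisation forces the arms to be similar on all four factors. A test that ignores three of them does not credit that balance, so its nominal variance is somewhat too large for the design and it tends to reject a little too rarely. If the omitted factors predict ulcers, the less-adjusted odds ratio also lies nearer to 1 than the adjusted one.

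The stakes are small but real. The section on the primary outcome measure defines the outcome as an ulcer at any point in the 24 months, so readers will set this odds ratio beside the Cox result. Precursors follow the primary endpoint's pattern, so the choice probably carries over to their any-event comparison, although they also receive the four-factor Cox analysis.

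**Working it through.** **1. Inputs from the Sample size section.** Control ulcer rate 20% over two years, hazard ratio 2.8 (control against intervention), two-sided 5% level, 80% power, 20% drop-out over two years, 147 patients required and 150 per arm planned.

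**2. The plan's own figure.** With exponential times, the control hazard and the drop-out hazard are each −ln(0.8)/2 = 0.1116 per year, and the intervention hazard is 0.1116/2.8 = 0.0398. The chance of an observed ulcer within two years is λ/(λ+δ) × (1 − exp(−2(λ+δ))), with δ the drop-out hazard:

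- control: 0.180
- intervention: 0.0688

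Then n = (1.960 + 0.842)² × (1/0.180 + 1/0.0688) / (ln 2.8)² = 148.8, or 149 per arm, within 2% of 147. The nQuery routine is not named; other log-rank approximations with the same drop-out give 120 to 141.

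**3. Events available.** 150 × 0.180 + 150 × 0.0688 = 27.0 + 10.3 = 37.3 ulcer patients.

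**4. Power of the two analyses.** Mantel-Haenszel by risk class was compared with logistic regression on arm and all four factors, in simulated trials of 300 patients. The document gives no prognostic effects, so these are assumed. Runs A to C use Pocock-Simon minimisation. Run A has 2,000 trials per scenario, an 85% biased coin, control rate 18%, treatment odds ratio 0.36 and risk-class odds ratio 3. Its moderate effects are odds ratios of 1.5 (gender), 1.3 per 10 years and 1.3 per vibration step; its strong effects are 2.0, 1.6 and 1.6. Run B repeats these scenarios with 3,000 trials each. Run D (1,000 trials) works on the hazard scale with balanced allocation within strata, risk-class hazard ratio 2.5, and moderate (1.3, 1.2 per 10 years, 1.5) or strong (1.8, 1.5 per 10 years, 2.5) effects for gender, age and neuropathy.

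| Effects of omitted factors | A | B (paired gain) | C | D |
|---|---|---|---|---|
| None | 80.2 → 81.0% | 0.7 (SE 0.2) | 80.1 → 80.7% | 83.5 → 84.1% |
| Moderate | 78.0 → 79.5% | 1.8 (SE 0.3) | 78.8 → 80.8% | 85.2 → 86.1% |
| Strong | 74.7 → 78.7% | 4.0 (SE 0.4) | 73.9 → 77.6% | 81.4 → 84.1% |

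The gains are 0.6 to 0.8 points with no effects, 0.9 to 2.0 with moderate and 2.7 to 4.0 with strong ones.

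**5. Type I error of the Mantel-Haenszel test.** Under minimisation: A 4.8 to 5.1%; B 4.5, 4.1 and 3.9% (Monte Carlo SE about 0.4); C 4.7, 4.7 and 4.3%. The logistic test gave 4.9 to 5.5% in A and 4.8 to 5.3% in B. In D, which does not use minimisation, Mantel-Haenszel gave 4.7 to 5.5%. In B, once both tests were set to the same size, the power gain fell to 0 to 0.3 points, so conservatism explains nearly all of it there.

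**6. Estimate and standard error (run D; no / moderate / strong effects).**

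| | Mantel-Haenszel by risk class | Four-factor logistic |
|---|---|---|
| Mean log odds ratio | −1.135 / −1.127 / −1.094 | −1.151 / −1.160 / −1.184 |
| Median SE | 0.392 / 0.391 / 0.387 | 0.395 / 0.397 / 0.404 |
| Ratio, absolute value | 2.90 / 2.88 / 2.83 | 2.91 / 2.92 / 2.93 |

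The standard error does not fall with adjustment. The estimate moves away from 1 by slightly more than the standard error grows. Run C shows the same shift: 0.37 to 0.39 against 0.35 when the omitted factors matter.

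**7. Odds ratio against hazard ratio.** The design hazard ratio is 1/2.8 = 0.357. From step 2, with no covariates at all, the odds ratio is (0.0688/0.9312)/(0.180/0.820) = 0.336. In run D the median Cox hazard ratio was 0.351 to 0.353, the Mantel-Haenszel odds ratio 0.328 to 0.344 and the logistic odds ratio 0.312 to 0.322.

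**The case against.** The best defence is that this analysis decides nothing. The adjusted Cox test is decisive and already carries all four factors; the odds ratio is an addition. Stratifying by risk class alone is also consistent with the plan's other simple summaries: the Wagner-grade comparison is split by risk class, and adverse events are tabulated by arm and risk class. A two-stratum Mantel-Haenszel analysis makes few assumptions and is valid, whereas a logistic model would have about 37.3/5 = 7.5 events per term. The power gain is near Monte Carlo error in the smaller runs unless strong effects are assumed.

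Most of this stands, and it keeps the point minor. It does not explain why any adverse event gets the four-factor model and any ulcer does not, and the event load is the same as in the planned Cox model.

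A reader might infer more than the document supports:

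- **That the odds ratio is less precise than it need be.** Step 6 shows the opposite direction: the standard error stays level or rises slightly with adjustment.
- **That the missing factors make the odds ratio not comparable with the Cox result.** The two measures differ whatever the covariates, because one ignores follow-up time. Adding the factors moves the odds ratio further from the hazard ratio (step 7).

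**Conclusion.** The point holds as a minor inconsistency with a small cost. The any-ulcer analysis omits three factors that were used for allocation and appear in every regression model of the plan. Its test is therefore slightly conservative and its odds ratio is drawn towards 1. The loss is under 1 point of power if the omitted factors do not predict ulcers, about 1 to 2 points for moderate effects and up to about 4 points for strong ones.

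These sizes rest on assumed prognostic effects and covariate distributions, and on the plan's own event rates. The conservatism is clearest in run B and weak in run A. The shift of the odds ratio reflects two differently adjusted quantities and is not evidence of bias in either. Nothing here biases the decisive Cox test, inflates type I error or threatens the trial's main conclusion.

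**What to change.** In the Primary endpoint part of the statistical analysis, name as the main any-ulcer odds ratio the one from logistic regression on treatment arm, age in years, gender, risk class and degree of neuropathy, with a 95% confidence interval. This is the model already specified for adverse events. Use it for the matching any-precursor comparison as well. Keep the crude rates by arm and risk class, and the Mantel-Haenszel estimate if wanted, as description.

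Do not extend the Mantel-Haenszel strata to all four factors instead. With two neuropathy levels that makes 16 cells for about 37 ulcer patients, and in run D 12 to 18% of patients fell in cells that contribute nothing.

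The cost is one sentence and no new data. The small downside is about 37 expected events for five terms, the load the Cox model already accepts.

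### The supplementary ulceration rates count patients who leave ulcer-free as non-events and so understate 24-month incidence; the decisive Cox test does not share this flaw

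*Protocol article*

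**What the plan says.** In the protocol article, Statistical analysis, Primary endpoint, the decisive analysis is a covariate-adjusted Cox regression of time to first ulcer in the intention-to-treat population. The adjusted hazard ratio with its 95% confidence interval is the effect estimator. As an addition in the same population, the section specifies ulceration rates per arm and a Mantel-Haenszel odds ratio stratified by risk class, "whereby the patients are included in the analysis regardless of the actual follow-up period". It states no person-time, censoring or imputation rule for that addition. The companion comparison of the highest Wagner grade gives grade 0 to patients without an ulceration, which points to the same handling of patients who leave early.

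The Sample size section expects early departures. It plans "with a drop-out rate of 20% over a two-year follow-up period per patient" and does not split this figure by arm. The Primary specific aim is to compare the incidence of foot ulcers over the study period, and the Primary outcome measure is any ulcer within 24 months after visit 0.

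**The concern.** A proportion that ignores follow-up estimates 24-month incidence only if everyone is followed for 24 months or has an ulcer first. A patient who leaves ulcer-free at month 2 is counted in the same way as one seen ulcer-free at month 24. The crude percentages must therefore fall below the true 24-month risk in both arms. If the arms lose patients at different rates, they fall by different amounts and the odds ratio moves as well.

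This matters because the hazard ratio carries no absolute risk, and these crude percentages are the only absolute ulcer rates the article specifies for an aim worded as a comparison of incidence. At stake is the accuracy of the reported absolute risks and, to a lesser degree, of a supportive odds ratio. The trial's formal conclusion is not at stake.

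**Working it through.** **Inputs, all from Sample size.** "type I error probability of 5% (two-sided) and a power of 80"%; "we assumed a 20% ulcer occurrence rate over two years" (control arm); "we assumed a hazard ratio of 2.8"; dropout 20% over two years. Enrolment is 150 per arm.

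**The plan's own figure first.** "Sample size calculations by use of log-rank test" led to this statement: "This resulted in a calculated required number of cases of 147". I read 147 as per arm, because 150 are then planned for one arm and 300 in total.

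- Intervention risk: 1 − 0.8^(1/2.8) = 0.0766.
- Freedman events: (1.960 + 0.842)² × (3.8/1.8)² = 7.849 × 4.457 = 34.98, so 35.
- Per arm without dropout: 35/(0.2000 + 0.0766) = 126.5, so 127.
- With the 20% dropout spread over K equal periods and leavers removed at the start of each: 149 (K = 2), 147 (K = 3), 145 (K = 4).

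The 147 is reproduced with K = 3. The article does not say how dropout was handled, so K is an assumption. Continuous exponential loss gives 141 and simple division by 0.8 gives 159. The check shows that the inputs are read as the plan intends.

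**Crude rates at 20% dropout in both arms.** Assume independent exponential ulcer and dropout times, with rates λ and γ per year. The proportion observed with an ulcer in two years is

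P = λ/(λ + γ) × [1 − e^(−2(λ + γ))].

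- γ = −ln(0.8)/2 = 0.1116.
- Control: λ = −ln(0.8)/2 = 0.1116, so P = 0.5 × (1 − 0.8 × 0.8) = 0.180, against a true 0.200.
- Intervention: λ = 0.1116/2.8 = 0.0398, so P = 0.2632 × (1 − 0.9234 × 0.8) = 0.0688, against a true 0.0766.
- If all leavers left at time 0, the rates would be 0.8 × 20.0% = 16.0% and 0.8 × 7.66% = 6.1%.

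**Odds ratio (intervention against control), equal dropout.**

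- Full follow-up: (0.0766/0.9234)/(0.20/0.80) = 0.332.
- With 20% dropout in each arm: (0.0688/0.9312)/(0.18/0.82) = 0.336.

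**Odds ratio with no true effect and unequal dropout (assumed scenarios).** Both arms have a true two-year risk of 20%. Rejection is a normal approximation to the unstratified two-sided comparison of proportions at 150 per arm.

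| Dropout control / intervention | Observed control | Observed intervention | OR | Rejection |
|---|---|---|---|---|
| 20% / 20% | 18.0% | 18.0% | 1.00 | 5.0% |
| 15% / 25% | 18.5% | 17.5% | 0.93 | 5.6% |
| 10% / 30% | 19.0% | 16.9% | 0.87 | 7.6% |

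For the last row, the control rate is 0.6793 × (1 − 0.8 × 0.9) = 0.1902 and the intervention rate is 0.3849 × (1 − 0.8 × 0.7) = 0.1693. The odds ratio is (0.1693/0.8307)/(0.1902/0.8098) = 0.87. With the arms exchanged, the two odds ratios become 1/0.93 = 1.07 and 1/0.87 = 1.15.

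**The Cox test in the same setting.** Trials were simulated with 150 per arm, no effect, and a Cox model with arm only, 1,500 per scenario. The average hazard ratio was 1.00 at 20%/20% and 0.99 at 10%/30%, with rejection of 4.5% and 4.1%. The Cox test therefore showed no inflation when dropout was unequal but unrelated to ulcer risk.

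**The case against.** The strongest reply is that the plan already handles unequal follow-up where it counts. The decisive test and the effect estimator come from a Cox model that censors leavers; the Mantel-Haenszel analysis is an openly declared addition. Crude proportions beside a Cox model are a common supplement, and they match an outcome worded as any ulcer in 24 months. Kaplan-Meier estimates may well appear in an analysis plan that is not shown.

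Most of this stands, and it limits the point to the absolute rates and a supportive odds ratio. It does not remove the point. The article fixes the rule of ignoring follow-up itself, and it specifies no other absolute ulcer risk.

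Several stronger readings are tempting but not supported:

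- A reader might infer that every dropout is counted as ulcer-free. Those who have an ulcer before leaving still count as events.
- A reader might infer that any dropout gap produces a serious false effect. The direction is right, but the sizes above are modest, and with equal dropout the odds ratio is almost unchanged.
- A reader might take the 72 active among 87 intervention patients (Trial status) as evidence of unequal dropout. That figure is device use, and no control figure is given. Ulcer status is assessed at the six-monthly visits in both arms, so a patient who stops measuring can remain in outcome follow-up.
- A reader might expect the crude rates to be the main published result. Nothing in the article gives them that status.
- A reader might extend the criticism to the adverse-event logistic model, "with the occurrence of at least one event per patient as the target". That section does not say that follow-up is ignored, and count models would change the question from patients affected to events per person-time. That is a choice between estimands and does not correct an error.

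**Conclusion.** The concern holds for the supplementary ulceration rates and, conditionally, for their odds ratio. At the plan's own 20% dropout, the crude rates understate 24-month incidence by about 2.0 percentage points in the control arm and 0.8 in the intervention arm. This rests on exponential times and on dropout unrelated to ulcer risk.

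Bias in the odds ratio needs unequal dropout, which the documents neither state nor exclude. With gaps of 10 and 20 points, the bias favours the arm losing more patients and is modest. The primary conclusion is not affected, provided censoring in the Cox model is non-informative. This is worth correcting as a matter of reporting; it is not a defect in the decisive analysis.

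**What to change.** In the Primary endpoint section, name the 24-month cumulative ulcer incidence per arm as the absolute-risk summary. Estimate it by Kaplan-Meier, or by Aalen-Johansen with death as a competing event. Report the risk difference with a 95% confidence interval, combined over risk classes 2 and 3. Keep the crude percentages and the Mantel-Haenszel odds ratio, labelled descriptive or supportive. Leave the adverse-event logistic model as planned.

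The cost is a change of wording and slightly more analysis, using the time-to-first-ulcer data already needed for the Cox model. The new estimates rest on the same assumption of non-informative censoring as the Cox model, so they do not protect against dropout that is related to ulcer risk.
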